### Data management and data analysis

Clinical and behavioral data will be collected via paper-based questionnaires and entered into the online Research Electronic Data Capture (REDCap) hosted at the Texas Woman’s University. All paper-based files will be coded and stored in a locked cabinet with files consisting of identifiable information (e.g. informed consent) kept separate from the clinical data. Kinematic data and neurophysiological data will be in electronic format. All electronic data will be stored on password-protected university servers. All data will be coded to ensure participant confidentiality throughout the study. The statistician and the principal investigator will review the data every three months to ensure completeness and data quality. The final de-identified dataset will be deposited to NICHD DASH for public access upon the completion of publications.

All data analyses will be performed in SPSS v28 (SPSS Inc., IBM, USA) by the biostatistician and significance will be set at p < .05. The percentages and patterns of missing data will be assessed to determine if pairwise deletion will be used for analysis or if an intention-to-treat strategy needs to be applied to replace missing values [57]. Comparison of baseline variables between groups will be conducted. If a baseline difference exists and judged to be a potential confound (e.g. baseline FSS score), the variable will be included as covariate in the primary analyses. Normality and outliers will then be checked to see if parametric analysis assumptions are met.

To examine effects on clinical, behavioral, and neurophysiological outcomes, we will perform a 2 group (anodal, sham) x 3 time point (baseline, post-intervention, follow-up) repeated measure ANOVA/ANCOVA. Resting state functional MRI data will be analyzed with a 2 group x 2 time point (baseline, post-intervention) ANOVA/ANCOVA. Post-hoc Bonferroni-adjusted comparisons will be completed if a main effect or interaction is detected. To examine whether individuals who show a greater change in neurophysiological outcomes demonstrate a greater reduction in PSF, Pearson or Spearman correlational analyses will be run to examine the relationship between changes in neurophysiological measures (input-output curve, fronto-striato-thalamic network connectivity) and changes in PSF (FSS). The strength of relationships will be interpreted as follows: r < 0.25 = little or no relationship; r of 0.25 to 0.5 = fair; r of 0.5 to 0.75 = moderate; and r > 0.7 = strong relationship [58].

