### Sample size estimation

Previous tDCS studies on pathological fatigue reported medium-large effect sizes (f > 0.35) [25,27,57,58]. A *prior* power analysis (G*Power version 3.1.9) using a more conservative effect size (f = 0.25), a power of 0.80, α-level at 0.05, and a correlation among the repeated measures of 0.5 indicate that a minimum of 28 participants is required for repeated measures analysis of variance (ANOVA). With consideration of a 10% attrition rate, a sample size of 32 (N = 16 per group) will be required.

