#### Clinical and behavioral assessments and outcomes.

The primary outcome for fatigue will be the Fatigue Severity Scale (FSS) score. FSS is a self-report questionnaire measuring the severity and impact of fatigue [41]. The FSS contains nine items rated on a 7-point Likert scale (1 = strongly disagree and 7 = strongly agree). The total score ranges from 9 to 63 with a higher score indicating greater fatigue. The FSS has been validated in chronic stroke [49]. Secondary measures of fatigue will be the Fatigue Scale of Motor and Cognitive Functions (FSMC) and Visual Analog Scale-Fatigue (VAS-F). The FSMC is a self-report questionnaire developed to measure cognitive and motor fatigue separately [50] and has been validated in chronic stroke [51]. The FSMC contains 20 items (10 for cognitive fatigue and 10 for motor fatigue) rated on a 5-point Likert scale. The total score ranges from 20 to 100 with a higher score indicating greater fatigue. The Visual Analog Scale-Fatigue (VAS-F) is a numerical scale ranging from 1-10 with a higher value indicating a higher level of global fatigue [52].

We previously showed that individuals with PSF reported high perceived effort during reaching and exhibited poor reach performance [16]. In the current study, we will adopt the same reaching task to evaluate changes in perceived effort and reach performance as a secondary measure of fatigue. At each assessment time point, participants will perform goal-directed reaches as fast and accurately as possible toward four targets that vary in distance and direction on a digitized tablet in sitting. Participants will also reach toward two central targets at both self-selected and fast speeds (i.e., as fast as possible) to evaluate the discrepancy between their movement choice (self-selected) and their capability (fast) [16]. Borg Rating of Perceived Exertion (Borg RPE) [53] and Paas Mental Effort Rating Scale (Paas MERS) [50] will be used to quantify perceived physical and mental effort associated with reaching, respectively. Borg RPE ranges from 6–20, with a higher value indicating greater perceived physical exertion. Paas MERS is a 9-point Likert scale that ranges from 1 (very, very low mental effort) to 9 (very, very high mental effort).

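### Intention-to-treat is made conditional on the observed missing data, with deletion as the alternative, so the three-visit primary analysis may be restricted to completers

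*Protocol article*

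**What the plan says.** The only text on analysis population and missing data is one sentence in the Protocol article, Data management and data analysis. The extent and pattern of missingness will be looked at "to determine if pairwise deletion will be used for analysis or if an intention-to-treat strategy needs to be applied to replace missing values". No threshold, decision rule or imputation method follows.

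The same section fixes the model: "we will perform a 2 group (anodal, sham) x 3 time point (baseline, post-intervention, follow-up) repeated measure ANOVA/ANCOVA". It applies to the primary behavioural outcome, of which Clinical and behavioral assessments and outcomes says: "The primary outcome for fatigue will be the Fatigue Severity Scale (FSS) score". Sample size estimation allows for loss: "With consideration of a 10% attrition rate, a sample size of 32 (N = 16 per group) will be required".

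On roles, Data management and data analysis states: "All data analyses will be performed in SPSS v28 (SPSS Inc., IBM, USA) by the biostatistician and significance will be set at p < .05". Under Randomization and blinding, the study biostatistician assigns participants and prepares the envelopes, and only participants and outcome assessors are said to be blinded.

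**The concern.** Intention-to-treat settles who is analysed and in which arm. It should not depend on what the data look like, and it is a separate decision from how missing values are handled. The sentence merges the two and makes both conditional: all randomised participants are kept only if the missingness seems to call for it, and otherwise values are deleted.

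Deletion also has a particular consequence here. A repeated-measures ANOVA over three visits uses only complete rows, so a participant who misses just the 1-month visit is removed from the post-intervention comparison too, although that FSS score was recorded. The first aim (end of the Introduction) concerns both a greater decrease in fatigue and its persistence to 1 month, so both comparisons are affected. If loss is related to response and differs between arms, the randomised comparison is distorted even at a visit where the data exist.

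**Working it through.** **1. The plan's own sample size.** Inputs from Sample size estimation: f = 0.25, power 0.80, alpha 0.05, correlation 0.5. Design: 2 groups, 3 visits. For the group x time interaction, lambda = N·m·f²/(1 − rho), df1 = (k − 1)(m − 1), df2 = (N − k)(m − 1).
- N = 28: lambda = 28 × 3 × 0.0625/0.5 = 10.5, df 2 and 52, power 0.812.
- N = 26: power 0.778. So 28 is the smallest even N that reaches 0.80.
- 28/0.90 = 31.1, which rounds up to 32 in equal groups.

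Both figures reproduce and the sample size is not in dispute.

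**2. How many are affected.** 0.10 × 32 = 3.2, so about 3 participants. This is an upper bound on those who lose a recorded post-intervention score, because anyone who leaves before that visit has none to lose.

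**3. Size of a possible bias.** Assumptions, none of them in the documents: no true effect; unit SD; correlation 0.5 between visits; everyone measured at post-intervention; loss before the 1-month visit of 50% among anodal participants whose post-intervention fatigue is more than 0.5 SD above the mean, and 3% among everyone else.
- Anodal loss: 0.5 × 0.3085 + 0.03 × 0.6915 = 0.175. Sham loss: 0.03. Overall: (0.175 + 0.03)/2 = 0.10, which matches the planned attrition.
- Mean post-intervention score of the remaining anodal participants: −(0.50 − 0.03) × 0.352/(1 − 0.175) = −0.20 SD, where 0.352 is the normal density at 0.5.
- Their baseline mean shifts by 0.5 × (−0.20) = −0.10 SD. The sham means do not shift.
- False benefit on change from baseline: −0.20 − (−0.10) = **−0.10 SD**.
- False benefit if baseline-adjusted (slope about 0.5): −0.20 − 0.5 × (−0.10) = **−0.15 SD**.
- Using all observed post-intervention scores: about **0**.

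A simulation of 8,000 trials with 16 per arm agrees. It gives a type I error of 0.058 for the interaction test in complete rows, against 0.052 without loss. The change-from-baseline figure belongs to the default ANOVA; the adjusted figure applies only if baseline FSS enters as a covariate, which the plan reserves for an observed baseline difference.

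**4. Other loss patterns** (10,000 simulated trials each; the replacement method is taken as last observation carried forward, because the article names none).

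| Loss at follow-up | Complete rows | Carried forward | More favourable of the two |
|---|---|---|---|
| Random, 10% | 0.047 | 0.048 | 0.059 |
| Random, 20% | 0.050 | 0.051 | 0.068 |
| Anodal only, more likely if fatigue worsened, 10% | 0.083 | 0.062 | 0.096 |
| Same, 20% | 0.159 | 0.069 | 0.175 |

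Entries are type I errors at a nominal 0.05. In the last two rows, the false difference in change from baseline to 1 month is −0.22 and −0.45 SD in complete rows, and −0.09 and −0.14 SD with carry-forward. When loss depends on outcome equally in both arms (about 10% each), the complete-row bias is about 0.

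**The case against.** A journal article may leave missing-data methods to an analysis plan. That covers silence, but here the article states a data-dependent rule, and a plan consistent with it would carry the same fault. Leaving out the imputation method and the sensitivity analyses would not by itself be a finding.

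Several other objections stand, at least in part:
- Harm needs loss that is both outcome-related and different between arms. The documents do not predict this. They offer five further sessions, all anodal, after the follow-up assessment and payment on completion, both of which favour return at 1 month.
- Under the first loss pattern the default interaction test barely moves (0.058). The larger error rates need all losses in one arm, and the largest also need twice the planned attrition.
- Pairwise deletion is a sensible term for the correlation analyses in the same section. It becomes complete-row deletion only in the three-visit ANOVA.

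A reader might also infer that an unblinded statistician will pick whichever method gives the better result. The documents do not show this. The sentence does not say who chooses, and its stated trigger is missingness, not the treatment effect. What can be said is that the biostatistician both assigns participants and runs the analyses, is not stated to be blinded, and is bound by no written rule that keeps the choice independent of allocation or results.

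**Conclusion.** The concern holds as a badly fixed rule: intention-to-treat is optional, confused with imputation, and set against a deletion method that restricts the primary FSS analysis to participants with all three visits. At the planned attrition this discards recorded post-intervention data from at most about 3 of 32 participants. Under the assumed one-arm, outcome-related loss, the false post-intervention benefit is about 0.10 SD for the plan's default analysis and 0.15 SD if baseline-adjusted. Under random loss each single method keeps its error near 5%, and taking the more favourable of two methods raises it to about 6% at 10% loss.

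These figures show direction and possible size and do not forecast this trial's bias. It would go too far to say that the primary comparison will be biased or that completers will be selected on outcome. The wording should be fixed, but the evidence does not make this a fatal flaw.

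**What to change.** In Data management and data analysis:

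1. State that all randomised participants are analysed in their allocated arm.
2. Delete the sentence that lets the missing-data pattern choose the method.
3. Name one primary method in advance. One suitable choice is a likelihood-based mixed model for repeated measures using all observed values (SPSS MIXED, in the software already named). Keeping baseline as one of the three time points means that a participant with only a baseline score still enters the model. Multiple imputation would also serve.
4. Keep complete-case analysis as a sensitivity analysis only.

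A mixed model deals with loss that depends on recorded scores, as in step 3 of the working. It cannot be relied on to remove bias from loss driven by unseen 1-month scores, as in the last two rows of the table.

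The cost is a change of wording and a slightly more complex model. No further participants or data are needed, and 28 inflated to 32 stands. Study design and setting expects data collection to end in July 2026, so the change should be dated and recorded before any analysis by arm.

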**Methods and analysis:**

This will be a double-blind randomized controlled trial targeting an enrollment of 32 participants with subacute-chronic stroke and significant fatigue (average Fatigue Severity Scale (FSS) > 4). Participants will be equally randomized to either anodal tDCS or sham tDCS groups. The anodal tDCS group will receive 20 minutes of 2-mA anodal tDCS applied to the ipsilesional primary motor cortex (M1) for five consecutive days. The sham tDCS group will receive the same protocol except there will be no active current delivered. Outcome assessments will take place at baseline (prior to randomization), immediately after the intervention, and at one-month follow-up. The primary behavioral outcome will be the FSS and the primary neurophysiological outcome will be an input-output curve of motor cortex excitability derived using transcranial magnetic stimulation. Secondary behavioral outcomes will include Fatigue Scale for Motor and Cognitive Function, Visual Analog Scale-Fatigue, Borg Rating of Perceived Exertion, and Paas Mental Effort Rating Scale. Secondary neurophysiological outcome will be the functional connectivity of the fronto-striato-thalamic network acquired using resting state functional Magnetic Resonance Imaging (MRI). Repeated measure ANOVA or ANCOVA will be conducted for all outcomes to compare the change between groups.

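### Baseline FSS is adjusted for only if the arms differ at baseline and the difference is judged a confound; always adjusting would cut the contrast variance by at least a quarter at the plan's own correlation

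*Protocol article*

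**What the plan says.** Under Data management and data analysis, the protocol first compares baseline variables between arms and then applies this rule to the primary analyses: "If a baseline difference exists and judged to be a potential confound (e.g. baseline FSS score), the variable will be included as covariate". The example it chooses is the baseline value of the primary outcome itself.

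The same section gives the model as a "2 group (anodal, sham) x 3 time point (baseline, post-intervention, follow-up) repeated measure ANOVA/ANCOVA", so baseline is one of the three outcome levels. Nothing says that this level is dropped when baseline FSS becomes a covariate. The abstract leaves the same choice open: "Repeated measure ANOVA or ANCOVA will be conducted for all outcomes to compare the change between groups".

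The Sample size estimation section plans on a repeated measures ANOVA with f = 0.25, "a power of 0.80", "α-level at 0.05" and "a correlation among the repeated measures of 0.5". It mentions no covariate, and arrives at 28 participants before attrition and 32 after.

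**The concern.** There are three problems with the rule.

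- **It answers the wrong question.** The arms are randomised, so a baseline difference is a chance event and does not show which covariates are worth adjusting for. Baseline FSS predicts later FSS whether or not the arms are balanced on it; the plan itself assumes a correlation of 0.5.
- **It makes the primary model depend on the data.** Whether the primary test is an ANOVA or an ANCOVA is settled by an observed difference plus a judgement, neither of which is defined. In a trial of 32, visible chance differences are common, so that discretion has room to matter.
- **When it fires, the model is badly specified.** If baseline FSS is both covariate and first outcome level, the residuals at that level are exactly zero. The error term then pools a level without variance with the two real follow-up levels.

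At stake is precision in a small trial, and a reader's confidence that the primary model was fixed in advance. Through the 2 x 3 model, the same rule reaches every repeated outcome.

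**Working it through.** **Inputs from the protocol.** f = 0.25, power 0.80, alpha 0.05, correlation rho = 0.5, two arms, three time points, N = 28 completers (14 per arm), 32 enrolled.

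**1. Reproduce the planned N.** For the group-by-time interaction under sphericity, the noncentrality is f² x N x m / (1 − rho) = 0.0625 x 28 x 3 / 0.5 = 10.5, on 2 and (28 − 2) x 2 = 52 df. Power is 0.812, so N = 28 reproduces. Then 28 / 0.9 = 31.1, rounded up to 32.

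**2. Translate the design effect.** Suppose the arms differ by 0, d, d SD at the three visits. The mean difference is 2d/3. The interaction effects are half the deviations from it: d/3, d/6 and d/6 in absolute size. Their mean square is (d²/9 + d²/36 + d²/36) / 3 = d²/18. So f = d/√18, and f = 0.25 gives d = 1.06 SD at both follow-ups. A pattern 0, d, 0 gives the same d.

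**3. Variance with and without baseline adjustment** (per person, in units of the outcome variance, compound symmetry):

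| Contrast | Change from baseline | Baseline-adjusted | Reduction |
|---|---|---|---|
| One follow-up | 2(1 − rho) = 1.00 | 1 − rho² = 0.75 | 25% |
| Mean of two follow-ups | (1 + rho)/2 + 1 − 2 rho = 0.75 | (1 + rho)/2 − rho² = 0.50 | 33% |

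The saving shrinks as the correlation rises. For one follow-up it is (1 − rho)/2: 35% at rho = 0.3, 25% at 0.5, 15% at 0.7 and 10% at 0.8.

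**4. Power at the design effect** (simulation, N = 28, d = 1.06 SD at both follow-ups, rho = 0.5, normal data, none missing):

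| Like-for-like comparison | Unadjusted | Adjusted |
|---|---|---|
| 2 df: planned interaction v adjusted test at both visits | 0.81 | about 0.92 |
| 1 df: mean of two follow-ups | 0.88 | 0.96 |
| 1 df: post-intervention only | 0.77 | 0.86 |

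At N = 32 the 1-df figures are 0.92 against 0.98 for the mean and 0.83 against 0.91 for post-intervention only.

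**5. The rule as written.** The protocol gives no trigger. If p < .05 on baseline FSS is assumed, the rule fires in about 5% of trials. Power is then 0.82 at N = 28 and 0.87 at N = 32, almost the same as never adjusting. Overall type I error is 0.043 to 0.044. Among null trials with such an imbalance, the unadjusted interaction test rejects about 16 to 17% of the time.

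**6. Baseline as both level and covariate.** If baseline is always entered in the three-level model, type I error is 0.050 to 0.052 and power at N = 28 is 0.90.

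**7. If the effect fades** (0, d, 0 with d = 1.06 SD, N = 28). The planned interaction has power 0.81, the adjusted 2-df test of both visits 0.82, and the adjusted 1-df test of their mean only 0.47.

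**The case against.** The best defence is that nothing here is invalid. Type I error is held overall, the planned N reproduces for the planned analysis, and baseline is not thrown away: as one of the three levels it already enters through within-person change. Using it twice is inelegant, but it does not break the interaction test. The trigger is undefined, so a 5% firing rate is an assumption. If the judgement were made on size, with 16 per arm a chance difference above 0.2 SD would occur in about 57% of trials and one above 0.5 SD in about 16%, so adjustment could be much more frequent. The gain also depends on the effect pattern. The Introduction reports that the benefit in an earlier single-session trial did not last to 1 month, and an average of the two visits would then do much worse than the planned test. Finally, an analysis plan that is not shown may settle the coding of the covariate.

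Most of this stands and limits the size of the point. It does not remove it. The protocol states a conditional rule, which is different from leaving a detail to a later document. The fading-effect argument tells against averaging the visits, not against adjusting for baseline: the adjusted test that keeps both visits matches the planned one in that case (0.82 against 0.81).

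A reader might take the 25% as a loss of a quarter of the attainable power. It is a variance figure for one follow-up. Comparing the planned 2-df interaction with a 1-df adjusted mean would also exaggerate the loss, because part of that gap comes from the change in degrees of freedom.

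**Conclusion.** The point holds as a should-fix. Entry of baseline FSS into the primary model depends on an observed chance difference and an undefined judgement, and the model as written would then carry baseline FSS on both sides. At rho = 0.5, leaving the adjustment out forgoes 25% of the contrast variance at one follow-up and 33% for the mean of two. That is roughly 10 points of power at the design effect with 28 completers.

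These figures assume compound symmetry, normal data, no missing values and an equal, sustained effect at both follow-ups. A higher correlation reduces the gain. With a fading effect, the adjusted two-visit test gains almost nothing over the planned one, but loses nothing either.

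Two stronger readings are not supported. The rule does not inflate overall type I error. The 16 to 17% rejection rate is conditional on an imbalance under an assumed p < .05 trigger, and describes the unadjusted test in the very trials where the plan may adjust. Nor can it be said that the trial would adjust only rarely, since that also rests on the assumed trigger.

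**What to change.** Before unblinding, amend the analysis section (or the analysis plan) as follows:

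- Delete the baseline-difference trigger as a rule for choosing covariates. A descriptive baseline table can stay.
- Always include the baseline value of the outcome as a covariate.
- Treat only the post-intervention and 1-month visits as outcomes, in a model with group, visit, group-by-visit and baseline value.
- Test the group effect at both visits, and not only their average, which loses power if the benefit fades by 1 month.
- Apply the same form to the other outcomes measured at all three time points. For connectivity, which is not measured at follow-up, use ANCOVA of the post-intervention value on the baseline value.

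This is a change of wording. It needs no new data or participants and costs one residual degree of freedom.

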Studies have suggested that PSF involves neural networks beyond M1 [20–22]. A pharmacological trial showed that functional connectivity of the fronto-striato-thalamic network predicted Modafinil induced PSF reduction [34]. Fronto-striato-thalamic network has been implicated in other pathological fatigue [35–37] and is likely to play a role in PSF [38]. Further, because the fronto-striato-thalamic network is anatomically and functionally connected to M1, altered M1 excitability after stroke is likely related to connectivity in this network [39,40]. Therefore, tDCS applied to M1, in addition to changing M1 excitability, might also modulate the fronto-striato-thalamic network and result in reduced PSF. Examining both brain excitability and connectivity might shed light on the underlying mechanism of PSF and the working mechanism of tDCS on PSF.

The purpose of this double-blind, randomized controlled trial is to investigate the effects of multiple sessions of anodal tDCS to ipsilesional M1 on PSF and underlying neurophysiology. We hypothesize that compared to the sham group, the anodal tDCS group will show a greater decrease in fatigue and the effect will last up to 1 month (Aim 1). We also hypothesize that compared to sham tDCS, anodal tDCS will significantly increase ipsilesional M1 excitability and the functional connectivity between ipsilesional M1 and the fronto-striato-thalamic network (Aim 2). Lastly, we hypothesize that individuals who show a greater change in the neurophysiological outcomes (M1 excitability, brain connectivity) will demonstrate a greater reduction in fatigue (Aim 3).

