### Participants

The inclusion criteria are: at least 18 years old; have a history of unilateral stroke ≥ 3 months prior to enrollment; have an average score ≥ 4 on the FSS [41]; have some movement capability in the more affected arm (Fugl Meyer Upper Extremity [42] ≥ 28) to ensure ability to perform the reaching task; and be able to follow three-step commands. Exclusion criteria are: acute medical problems; presence of any contraindication to tDCS, MRI or TMS; significant pain that interferes with arm movements; use of medication which may affect the level of fatigue; and presence of significant depression (Patient Health Questionnaire-9 > 10) [43].

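### Post-hoc comparisons may open on any main effect, and no sentence names the group × time term as the test of efficacy

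*Protocol article*

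**What the plan says.** The protocol article, under Data management and data analysis, plans a "2 group (anodal, sham) x 3 time point (baseline, post-intervention, follow-up) repeated measure ANOVA/ANCOVA" for clinical, behavioural and neurophysiological outcomes. Resting-state MRI has a 2 × 2 version, since it is not repeated at follow-up. The same paragraph adds that "Post-hoc Bonferroni-adjusted comparisons will be completed if a main effect or interaction is detected". The general level is given as "significance will be set at p < .05".

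The question these models serve appears elsewhere. The abstract says "Repeated measure ANOVA or ANCOVA will be conducted for all outcomes to compare the change between groups". In the Introduction, Aim 1 is that, compared with sham, "the anodal tDCS group will show a greater decrease in fatigue and the effect will last up to 1 month". Aim 2 is likewise framed as anodal against sham.

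The article does not say which of the three omnibus terms (group, time, group × time) decides efficacy. Nor does it say which pairs the post-hoc comparisons cover.

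**The concern.** Three terms can open the post-hoc step, and they do not answer the same question.

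- **Group × time** compares change between arms. This is what the abstract and Aims 1 and 2 ask.
- **Time** asks whether the outcome moves, averaged over arms. It can be significant when tDCS does nothing. Entry requires participants to "have an average score ≥ 4 on the FSS", so selection is on the primary outcome scale and regression to the mean is plausible. Both arms also attend five daily sessions, and enrolment may begin three months after stroke.
- **Group** averages the arm difference over all three visits, including baseline.

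The risk lies in what may follow a significant time effect. If time points are then compared separately within each arm, one arm can cross the threshold and the other miss it by chance, and the result can be taken for a treatment effect. Bonferroni adjustment does not prevent this. It limits the error of each within-arm test and does not control the contrast between arms.

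**Working it through.** **Inputs from the protocol (Sample size estimation).** f = 0.25; "a power of 0.80, α-level at 0.05, and a correlation among the repeated measures of 0.5"; minimum N = 28; 32 enrolled, 16 per arm. The check uses 14 per arm (28 analysed) and 16 per arm.

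**The plan's own figure.** For the within-subject or interaction F test with m = 3 visits, λ = f² × N × m / (1 − ρ) = 0.0625 × 28 × 3 / 0.5 = 10.5, with 2 and 2 × (28 − 2) = 52 degrees of freedom. Power is 0.812; N = 26 gives 0.778. So 28 reproduces, and 28 / 0.9 = 31.1, which rounds up to 32 for two equal arms. The sample size already fits the interaction and is not affected by this point.

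**Group main effect.** If tDCS shifts the outcome by δ at both later visits and by nothing at baseline, the group term estimates (0 + δ + δ) / 3 = 2δ/3. It is unbiased for zero when δ = 0, so it is a valid test, but one third of the effect is lost.

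**Simulation.** 40,000 trials per setting; normal data; correlation 0.5; no tDCS effect. *Assumed:* the same fall d (in SD units) in both arms at both later visits, and Bonferroni over three comparisons. The step opens if group, time or interaction has p < 0.05. Two-sided paired t tests against baseline then follow within each arm.

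| Shared fall d (SD) | Step opens, 14 / 16 per arm | Fall in anodal only, one or both later visits, 14 / 16 per arm | Fall in anodal only, post-intervention, 16 per arm | Anodal only, one or both visits, interaction as sole gate, 16 per arm |
|---|---|---|---|---|
| 0 | 14% / 14% | 1% / 1% | 0.6% | 0.5% |
| 0.3 | 40% / 44% | 11% / 13% | 7.4% | 1.9% |
| 0.5 | 78% / 84% | 28% / 32% | 19.6% | 2.7% |
| 0.7 | 97% / 99% | 39% / 39% | 24.9% | 2.7% |
| 1.0 | 100% / 100% | 24% / 17% | 9.8% | 1.7% |
| 1.2 | 100% / 100% | 10% / 5% | 2.7% | 0.7% |

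The interaction itself is significant in about 5% of trials in every row. At 14 per arm and d = 0.3 / 0.5 / 0.7, the misleading pattern comes with a non-significant interaction in 9% / 25% / 37% of trials, which is most of the 11% / 28% / 39%.

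**Why it peaks.** With ρ = 0.5 the SD of a change is √(2 × (1 − 0.5)) = 1, so each within-arm t test has noncentrality d√n. At d = 0.7 and n = 16 this is 0.7 × 4 = 2.8. With 15 degrees of freedom and critical value 2.694, power is 0.555. The arms are independent, so anodal only has probability 0.555 × 0.445 = 0.247 at one visit, matching 24.9%. The product p(1 − p) cannot exceed 0.25 and shrinks when p is near 0 or 1.

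**Sensitivity.** Bonferroni over six at 16 per arm, post-intervention: 5.0%, 15.3%, 24.9%, 15.0% and 5.4% for d = 0.3, 0.5, 0.7, 1.0 and 1.2. With ρ = 0.7, d = 0.5 and Bonferroni over three: 24.8%. If the post-hoc tests compare the arms directly, at each visit or on change, false positives are 2.4% to 4.8%.

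**The case against.** The strongest reply is that the harmful step is not in the text. The analysis section does not mention within-arm tests. By common convention each post-hoc test follows its own term: a time effect leads to time points compared with arms pooled, and an interaction leads to simple effects. On that reading a shared fall yields only the true statement that fatigue fell. The abstract and Aim 1 already frame success as a difference from sham, and nothing permits significance in one arm alone to count as efficacy. The exact comparison family may also properly sit in a fuller document.

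Much of this stands. A reader might infer that the protocol prescribes within-arm tests, or that it would claim efficacy after a null interaction. It says neither. The 14% in the first row might be read as a false-efficacy rate; it is only the chance that any of three omnibus tests is significant when nothing changes. A reader might also conclude that neither main effect tests treatment. For group that is wrong: under randomisation it is a valid test, though diluted.

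The pooled reading does leave part of the rule empty, however. Group has two levels, so a pooled comparison after a group effect repeats it. In the 2 × 2 MRI model this holds for both factors. There, a post-hoc test after a main effect adds information only if split by arm or by visit, so the within-arm reading is natural. The opening rule is itself stated in the article, so it is not a detail left for elsewhere.

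**Conclusion.** The concern holds in a conditional form. The stated rule opens post-hoc testing on terms that do not address the between-arm difference in change, and no sentence names the term that does as decisive. Whether this misleads depends on which comparisons follow. If they are within-arm, a fall shared by both arms gives a significant fall in anodal but not in sham in about 5% to 39% of trials with no tDCS effect (falls of 0.3 to 1.2 SD, ρ = 0.5, 14 to 16 per arm, Bonferroni over three, one or both later visits). The peak is near 0.7 SD, and the rate is about 1% if nothing changes. With the interaction as sole gate it is at most about 3%. With direct between-arm tests false positives stay below 5%, and pooled time comparisons cannot produce the pattern. The size of the shared fall, its equality at both visits and the Bonferroni family are assumptions; the protocol gives none of them.

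**What to change.** Replace the post-hoc sentence with wording such as: *Efficacy is judged only by the between-arm difference in change: the group × time term, or the between-arm contrast at the post-baseline visits if baseline is a covariate. Follow-on tests are the between-arm differences in change at post-intervention and at one month, Bonferroni-adjusted for two. For the MRI outcomes there is one between-arm contrast, at post-intervention, without this adjustment. Main effects of time and within-arm changes are descriptive and are not evidence of efficacy.*

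The covariate clause is needed because, in an ANCOVA whose repeated levels are only the later visits, a sustained treatment effect appears in the group term. The MRI clause is needed because that outcome has a single post-baseline visit.

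The change is a few lines of text, with no new data and no change to the 28 or 32. Its price is that within-arm p-values can no longer support an efficacy claim. It should be settled before unblinded data are analysed.
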